#### ***Secondary outcomes***

1) Condomless anal intercourse with men and multiple male sex partnerships in the past six months measured at Month 6.

2) Uptake of other types of HIV testing in the past six months measured at Month 6. They are a) HIV testing at CBOs in Hong Kong, b) HIV testing at public hospitals/clinics in Hong Kong, c) HIV testing at private hospitals/clinics in Hong Kong, d) HIV testing at other organizations in Hong Kong, and e) HIV testing in places other than Hong Kong.

### ***Baseline background characteristics***

Information on social demographics (i.e., age, current relationship status, education level, income), sexual orientation, history of HIV testing, COVID-19, and other sexually transmitted infections will be collected. In addition, participants are asked to report the use of pre-exposure prophylaxis and different HIV or sexually transmitted infection prevention services (receiving free condoms, peer education and pamphlets, and attending workshops).

### ***Process evaluation***

At Month 6, participants will be asked about their level of satisfaction with the promotion and implementation of HIVST-Chatbot/HIVST-OIC.

## Statistical analysis

Intention-to-treat analysis will be performed. Multiple imputations will handle missing values at Month 6. Markov Chain Monte Carlo method will be used to impute data with the arbitrary pattern of missing values, while monotone methods are used to impute data having a monotone pattern of missing values. Predictors included baseline background characteristics and baseline values of these outcomes. The relative risk reduction, absolute risk reduction, and number needed to treat, and their 95% confidence interval will be calculated using Excel. The chi-square tests will inspect between-group balances of potential confounders at baseline. Adjustments will be made if any potential confounders show  $P < .05$  in the comparisons. SPSS 26.0 for Windows (SPSS Inc., Chicago, IL) will be used for all analyses; statistical significance is set at the  $P < .05$  level (one-sided).

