#### Methods

A parallel-group non-inferiority RCT will be conducted. Participants are Chinese-speaking MSM aged 18 years or above with access to live-chat applications. A total of 528 participants will be recruited through multiple sources, including outreach in gay venues, online advertisement, and peer referral. After completing the baseline telephone survey, participants will be randomized evenly into the intervention or control groups. Participants in the intervention group will watch an online video promoting HIVST-Chatbot and receive a free HIVST kit. The Chatbot will contact the participant to implement HIVST and provide standard-of-care and real-time pre-test and post-test counseling, and instruction on how to use the HIVST kit through WhatsApp. Participants in the control group will watch an online video promoting HIVST-OIC and receive a free HIVST kit in the same manner. Upon appointment, a trained testing administrator will implement HIVST and provide standard-of-care and real-time pre-test and post-test counseling and instruction on how to use the HIVST kit through live-chat applications. All participants will complete a telephone follow-up survey six months after the baseline. The primary outcomes are HIVST uptake and the proportion of HIVST users receiving counseling support along with testing in the past six months measured at Month 6. Secondary outcomes include sexual risk behaviors and uptake of HIV testing other than HIVST during the follow-up period. Intention-to-treat analysis will be used.

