## Methods

### Study design

A parallel-group non-inferiority randomized controlled trial will be conducted. A total of 528 participants are randomized 1:1 to either the intervention group (n=264) or the control group (n=264). We will promote and implement HIVST-Chatbot and HIVST-OIC in the intervention group and control group, respectively. A telephone follow-up evaluation will be conducted six months after the baseline survey by blinded interviewers. The study was registered at ClinicalTrial.gov (number NCT05796622). A flowchart diagram is shown in Figure 1.

[figure not shown]

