### **Sample size planning**

The target sample size is 528 (264 per group). Our previous study showed that about 90% of MSM used HIVST after exposure to HIVST-OIC promotion and implementation. We conservatively assume that 80% of participants in the control group will take up HIVST during the project period. A non-inferiority margin of between-group difference of this primary outcome is set at 10% (no worse than 10% less than that of the control group). A sample size of 198 per group will be sufficient to confer 80% power at the one-sided significance level of 0.05 (PASS 11.0). Given the 25% drop-out rate during the follow-up period, 264 participants per group (528 total) will be needed for the study.

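### Missing Month 6 HIVST uptake is imputed from baseline variables only, leaving out the service-use records kept in both arms; if non-testers drop out more, false non-inferiority can exceed 5%.

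*Protocol*

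**What the plan says.** The Protocol's Statistical analysis section plans an intention-to-treat analysis and states one way of dealing with absent outcomes: "Multiple imputations will handle missing values at Month 6". It then names the imputation variables: "Predictors included baseline background characteristics and baseline values of these outcomes". Neither treatment arm nor any information gathered after randomisation is on that list.

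The outcome comes from a single contact: "All participants will complete a telephone follow-up survey six months after the baseline" (Abstract, Methods). Sample size planning expects a quarter of the men to be lost: "Given the 25% drop-out rate during the follow-up period". The non-inferiority margin is 10 percentage points.

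The Primary outcomes section adds that the Chatbot logs each use of its service and that testing administrators log each HIVST-OIC session. Use of the trial services is therefore recorded in both arms whether or not a man answers the Month 6 call. The Protocol does not link these records to missing outcomes.

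**The concern.** Imputation from baseline data is unbiased only if, among men with the same baseline values, missing the call is unrelated to having self-tested. Here the outcome is itself engagement with an offered service. A man who ignores the kit may well ignore the telephone too, and engagement after randomisation is not a baseline variable. The Protocol neither measures nor excludes such a link.

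If it exists and works alike in both arms, the arm with more non-testers loses more of them. Responders then overstate uptake in both arms, and more so in the worse arm. The observed deficit shrinks, which in a non-inferiority trial favours success. Imputing correctly within each arm does not remove this. The records that would tell the analyst most about a missing outcome are collected but left out of the predictor list.

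**Working it through.** **The plan's own figure.** Inputs from Sample size planning: "We conservatively assume that 80% of participants in the control group will take up HIVST during the project period"; the same 80% in the Chatbot arm; margin 0.10; one-sided 5%; 80% power.

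n = (1.645 + 0.842)² × (2 × 0.80 × 0.20) / 0.10² ≈ 197.8, so 198 per group. Then 198 / 0.75 = 264. Both stated figures reproduce.

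**Method.** Set the truth at the margin: p = 0.80 (control) and 0.70 (Chatbot), with 264 per arm. Let r₁ and r₀ be the retention of testers and non-testers. These are assumptions, because the Protocol gives neither.

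- Responder uptake = p·r₁ / [p·r₁ + (1 − p)·r₀]
- P(declare non-inferior) = Φ[(0.10 − responder difference)/SE − 1.645], with unpooled SE

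Baseline predictors are taken to explain none of the link, so imputation reproduces the responder rate. With drop-out unrelated to testing the result is 5.0%.

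**Worked example, r₁ = 0.80 and r₀ = 0.55 in both arms.**

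- Control: 0.640/0.750 = 85.3%, with 198 responders.
- Chatbot: 0.560/0.725 = 77.2%, with about 191 responders.
- Difference 8.1 points and SE 0.0394, so Φ(0.485 − 1.645) = Φ(−1.16) = 12.3%.

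Simulating proper by-arm multiple imputation (20 imputations, Rubin's rules) gives 12% to 13%.

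**Range.** Let non-testers be k times as likely to drop out, with the same rates in both arms and 25% lost overall. Tester drop-out is then 0.25/(0.75 + 0.25k).

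| k | Tester / non-tester drop-out | Responder difference (points) | False non-inferiority |
|---|---|---|---|
| 1 | 25% / 25% | 10.0 | 5.0% |
| 1.5 | 22.2% / 33.3% | 9.2 | 7.3% |
| 2 | 20% / 40% | 8.5 | 10.0% |
| 2.5 | 18.2% / 45.5% | 7.9 | 13.3% |
| 3 | 16.7% / 50% | 7.4 | 17.0% |
| 4 | 14.3% / 57.1% | 6.5 | 25.4% |

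**Sensitivity to the assumptions.**

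- Each arm loses exactly 25%: 7.9% at k = 2 and 9.0% at k = 3, which is about the maximum.
- True uptake 90% versus 80%: 16.6% at k = 2. Sample size planning describes its 80% as conservative against about 90% in the earlier study.
- Reversal: responders at 80.0% and 69.5%, with drop-outs testing at 0.8 of the responder rate in both arms. True uptake is the responder rate × (0.75 + 0.25 × 0.8) = × 0.95, giving 76% and 66%. The responder difference is 10.5 points and false non-inferiority falls to 3.9%.

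**What the service records would do (80%/55% example).** Suppose the records identify a share s of testers, and that missing men without a record are imputed from responders without one, by arm.

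- s = 0.7, control: unrecorded testers are 0.24 of the arm and non-testers 0.20. Responders without a record test at 0.192/(0.192 + 0.110) = 63.6%. Missing men without a record are 0.048 + 0.090 = 0.138 of the arm, of whom 0.048 tested. Overstatement: 0.138 × 0.636 − 0.048 = 4.0 points.
- s = 0.7, Chatbot: 0.168/(0.168 + 0.165) = 50.5%. Overstatement: 0.177 × 0.505 − 0.042 = 4.7 points.
- The difference becomes −10 + (4.7 − 4.0), about −9.3 from these rounded figures (−9.2 unrounded), instead of −8.1.

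Simulated false non-inferiority is about 7.5% at s = 0.7 and about 5% at s = 0.9. Power at equal uptake of 80% is about 84% to 85%, against about 87% to 88% without the records.

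**The case against.** The strongest objection is that sensitivity analyses for missing data usually sit in the SAP, which is not at hand. That stands: a reader might infer that the trial has no such analysis, and the Protocol cannot show it. The predictor list, however, is stated in the Protocol and can be judged as written.

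Second, a reader might take 12% to 13% as the trial's error rate. The documents do not support that. The figure depends on assumed retention of 80% and 55%, and on a Chatbot arm that loses 27.5% rather than the planned 25%. It also gives no credit to baseline history of HIV testing, PrEP use or use of prevention services, any of which may explain part of the link.

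Third, a reader might infer that extra drop-out among non-testers always shrinks the arm difference. The reversal case shows that it does not. Shrinkage follows when tester-specific retention is the same in both arms, and that is an assumption.

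Fourth, a fixed pass rule, such as surviving a 20-point downward shift in both arms, would be a preference and a weak correction. In the 80%/55% example it lowers control by 0.25 × 20 = 5.0 points and Chatbot by 0.275 × 20 = 5.5 points, so the estimate moves only from −8.1 to −8.6. Simulated error is then 7.6%, still above 5%, with about 80% power.

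Finally, arm is absent from the predictor list, but the Protocol does not say imputation ignores arm. If it did, simulated error would be 9.2% even with random loss, which is reason to state the point.

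**Conclusion.** The point holds as a badly fixed choice of imputation predictors, not as proof of an inflated error rate. With same-in-both-arms drop-out 1.5 to 4 times as high in non-testers, 25% overall loss, true uptake of 80% versus 70% and uninformative baseline variables, false non-inferiority is about 7% to 25% against a nominal 5%. It is at most about 9% if each arm loses exactly 25%, and below 5% under some other mechanisms. Neither size nor direction can be settled from the Protocol. With a quarter of outcomes expected to be missing, the non-inferiority claim should not rest on baseline data alone when more informative records exist in both arms. The change is worth making; confidence in any one figure is no more than moderate.

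**What to change.** In the Statistical analysis section:

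1. State that imputation is done separately by arm, and add the Chatbot and administrator service-use records as predictors of missing HIVST uptake. The outcome is any HIVST and the records cover only the trial services, so they inform a missing value without replacing it.
2. Keep multiple imputation as the main analysis. Add a delta-adjusted tipping-point analysis that lowers imputed uptake (a) in both arms and (b) in the Chatbot arm only. Report the shift at which the lower confidence limit crosses −10 points, without a fixed pass threshold. If the SAP already contains this, cite it.

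Counting every missing man as a non-tester is not a safe substitute. With 25% random loss it shrinks a true 10-point deficit to 0.75 × 10 = 7.5 points, and simulated false non-inferiority is 14.6%.

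The cost is a few lines of text and code, linkage of records already being kept, and possibly a less favourable claim. No new data collection is needed.

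### The listed imputation predictors leave out randomised group; read as the complete list, they shrink the between-group difference towards zero, which favours non-inferiority

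*Protocol*

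**What the plan says.** The Statistical analysis section of the protocol states: "Intention-to-treat analysis will be performed". On missing data it continues: "Multiple imputations will handle missing values at Month 6". It names a Markov chain Monte Carlo method for arbitrary missingness patterns and monotone methods for monotone ones, and then the predictors: "Predictors included baseline background characteristics and baseline values of these outcomes".

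The section Baseline background characteristics defines the first of those two groups: "Information on social demographics (i.e., age, current relationship status, education level, income), sexual orientation, history of HIV testing, COVID-19, and other sexually transmitted infections", followed by use of pre-exposure prophylaxis and of prevention services. Allocation is not in that list and is not a baseline value of an outcome. No other section says that allocation enters the imputation or that the arms are imputed separately.

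The amount of imputation to expect comes from Sample size planning: "Given the 25% drop-out rate during the follow-up period", 264 per group are to be recruited. The same section sets the comparison: "A non-inferiority margin of between-group difference of this primary outcome is set at 10% (no worse than 10% less than that of the control group").

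**The concern.** An imputation model should contain every term whose effect the analysis will estimate, and here that is the randomised group. If group is left out, missing outcomes in both arms are drawn from one common model. Baseline variables cannot stand in for group, because randomisation makes them independent of it. In expectation, the imputed participants therefore add no difference between arms, and the overall difference is diluted in proportion to how many are imputed.

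In a superiority trial this dilution would be conservative. Here the claim is that the Chatbot is not more than 10 points worse, so pulling the estimate towards zero makes that claim easier to reach when it is false. The protocol's Conclusions section would carry a non-inferior result into routine services.

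**Working it through.** **Inputs.** From Sample size planning: control uptake 80%, margin 10 points, one-sided 0.05, power 80%, 198 evaluable per group, 25% drop-out, 264 randomised per group. The one-sided 0.05 level is repeated in Statistical analysis. Assumed for the check: outcomes missing at random at the same rate in both arms, the listed predictors being the complete list, and true Chatbot uptake of 70%, exactly at the margin.

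**1. The plan's own figure.** n = (1.645 + 0.842)² × (0.8×0.2 + 0.8×0.2) / 0.10² = 197.8, so 198 per group. Then 198 / 0.75 = 264. Both figures reproduce.

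**2. Expected estimate without group.** The common imputed rate is (0.80 + 0.70)/2 = 0.75.
- Control: 0.75×0.80 + 0.25×0.75 = 0.7875
- Chatbot: 0.75×0.70 + 0.25×0.75 = 0.7125
- Difference: −0.075, which is 0.75 × (−0.10)

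**3. False non-inferiority by normal theory (many imputations).**
- Within-imputation variance: (0.7875×0.2125 + 0.7125×0.2875)/264 = 0.001410
- Between-imputation variance, with 66 imputed per arm: 2×66×0.75×0.25/264² = 0.000355
- Rubin standard error: √0.001765 = 0.0420
- True spread of the estimate: 0.75 × √[(0.16 + 0.21)/198] = 0.0324
- Non-inferiority is declared if the estimate exceeds −0.10 + 1.645×0.0420 = −0.0309
- Probability: 1 − Φ[(−0.0309 + 0.075)/0.0324] = 1 − Φ(1.36) = 8.7%

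The Rubin standard error is larger than the true spread, and this offsets part of the bias but not all of it.

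**4. Simulation** (20,000 to 40,000 trials per setting; 5, 20 or 100 imputations; Rubin's rules; 80% against 70%; 25% missing).

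| Imputation model | Mean estimate | False non-inferiority, one-sided 5% | Same, two-sided 95% interval |
|---|---|---|---|
| Group omitted | −7.5 points | 8.7 to 9.1% | 4.1 to 4.2% |
| Group included | −10.0 points | 5.1 to 5.3% | 2.5 to 2.7% |

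A separate run gave 9.0% against 4.9% (one-sided 5%) and 4.0% against 2.6% (95% interval).

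**5. Dependence on the amount missing** (group omitted, one-sided 5%).

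| Missing | 5% | 10% | 15% | 20% | 25% | 30% | 40% |
|---|---|---|---|---|---|---|---|
| False non-inferiority | 5.5% | 6.0% | 7.0% | 7.8% | 8.8% | 10.1% | 12.9% |

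The separate run gave 6.6% at 10% missing. With group included, the rate stayed between 4.9% and 5.2% throughout.

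**6. Other settings** (group omitted, one-sided 5%). With 20% missing in control and 30% in the Chatbot arm, the rate is 9.2%. With uptake of 90% against 80% and 25% missing, it is 12.5%. With a strongly prognostic baseline covariate in the model (uptake 15 points above or below the mean), the estimate is still −7.5 points and the rate 9.9%, against 4.9% with group included. Good baseline predictors do not repair the omission.

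**The case against.** The strongest objection is that the sentence is open. It does not say that these are the only predictors, and it does not say that the arms are pooled. Imputing within each arm from exactly these predictors fits the wording and removes the problem, and a statistical analysis plan that is not at hand may say so. This stands in part: pooled imputation is the consequence of reading the list as complete, not something the protocol asserts. It does not dispose of the point, because the protocol chose to give a list, allocation is absent from it, and a statistician who follows the text as written would produce the bias.

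A second objection is that the error rate is conditional, and this stands fully. The 25% is a planning allowance, the 9% applies to a true deficit exactly at the margin, and it uses the one-sided 5% level. The only interval that the protocol mentions is 95%. If that interval decides, the rate is about 4%, which is below the stated one-sided 5% although still above the 2.5% that the interval should give.

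A reader might also infer three stronger points that the documents do not support:
- **That intention-to-treat analysis with missing-at-random imputation itself leans towards no difference.** With group in the model, the simulated estimate is −10.0 points and the error about 5%. The lean comes from leaving group out.
- **That the protocol is deficient for lacking a sensitivity analysis for data not missing at random, or for not using service records as predictors.** The first is commonly left to the statistical analysis plan and the second is a preference.
- **That the planned power is overstated.** It rests on 198 completers per group, reproduces exactly, and takes no credit for imputation.

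**Conclusion.** The concern holds in conditional form. The stated predictor list omits randomised group and no section supplies it. If the list is complete, the estimated difference shrinks by the missing fraction. At the planning values, a true 10-point deficit is estimated as about 7.5 points, and false non-inferiority is about 9% instead of about 5%. At 10% missing it is about 6 to 6.6%. With a two-sided 95% interval it is about 4% against 2.5%.

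These figures assume outcomes missing at random and cover HIVST uptake only. The second primary outcome, counseling among users, was not calculated. The problem disappears if imputation is done by arm or includes group. It is still worth correcting before analysis, because the text as it stands leads to a bias in favour of the trial's own claim.

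**What to change.** In Statistical analysis, state that multiple imputation is carried out separately by randomised group, or that randomised group is included in the imputation model, and keep the listed baseline predictors in either case. If a statistical analysis plan exists, give it the same wording.

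The cost is one sentence. It needs no new data and no change to the sample size, which already rests on completers.

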### **The baseline survey and random allocation process**

Participants will be randomized evenly to either the intervention or control groups. Computer-generated random allocation codes will be produced and sealed in opaque envelopes by a research staff member without involvement in recruitment or baseline survey. One envelope will be drawn and opened by the fieldworkers. They will then inform the participant which group he is assigned to. Block randomization with a block size of eight will be used.

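### Covariate adjustment is triggered by baseline significance tests, so chance picks the covariates, and the plan does not say whether the adjusted or the unadjusted difference decides non-inferiority

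*Protocol*

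**What the plan says.** The rule is in the protocol's Statistical analysis section: "The chi-square tests will inspect between-group balances of potential confounders at baseline", and then "Adjustments will be made if any potential confounders show" a P value below .05. The section does not list the variables to be tested or name an adjusted model. It does call for an absolute risk reduction with a 95% confidence interval, and does not tie that calculation to the balance tests.

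The candidates appear to be the items listed under Baseline background characteristics. One sentence there covers "Information on social demographics (i.e., age, current relationship status, education level, income), sexual orientation, history of HIV testing, COVID-19, and other sexually transmitted infections". A second one says that "participants are asked to report the use of pre-exposure prophylaxis and different HIV or sexually transmitted infection prevention services".

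On allocation, the protocol states 1:1 randomisation and "Block randomization with a block size of eight will be used". It names no stratification factor, so the design itself brings no covariate into the analysis. The only unconditional use of baseline data is in the multiple imputation: "Predictors included baseline background characteristics and baseline values of these outcomes".

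**The concern.** If allocation is carried out as described, any baseline difference between the groups as randomised arose by chance. A balance test at P < .05 then tests a null hypothesis that is already known to hold. What matters for the treatment comparison is how strongly a covariate relates to the outcome, and the test says nothing about that. A strong predictor of uptake has the same small chance of being selected as an irrelevant item.

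Two things are at stake. First, the form of the primary comparison depends on the data, and the text does not say which result governs when an adjusted and an unadjusted difference both exist. In a non-inferiority trial with one margin, that should be settled before outcomes are seen. Second, precision available from data already being collected is mostly given up.

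**Working it through.** **Reproducing the plan's figure.** Inputs from Sample size planning: 80% uptake in the control group, margin 10 points, one-sided alpha 0.05, power 80%. Equal true uptake in the Chatbot group is assumed here.

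n per group = (1.645 + 0.842)² × 2 × 0.80 × 0.20 / 0.10² = 197.9, rounded up to 198. With 25% dropout, 198 / 0.75 = 264. Both figures agree with the protocol. The calculation takes no credit for covariates, so it does not depend on the adjustment rule.

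**Selection of a single covariate.** Under randomisation each test has about a 5% chance of P < .05, whatever the covariate's prognostic value. Any given covariate is therefore left out about 95% of the time. The simulation below gave trigger rates of 5.0% to 5.1%.

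**Chance that adjustment is triggered at all.** For k independent items this is 1 − 0.95^k. The first part of the baseline list gives about 8 items. Adding pre-exposure prophylaxis and the prevention services gives about 12 or 13. Fifteen allows for a few more, such as baseline values of the outcomes.

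- k = 8: 34%
- k = 12: 46%
- k = 13: 49%
- k = 15: 54%

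Both the count and the independence are assumptions.

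**Effect on power and type I error.** A simulation used 198 per group, 200,000 trials per setting, and one binary predictor with 50% prevalence and mean uptake 80%. It compared the unadjusted difference, the trigger rule, and a risk difference always stratified by the predictor. Predictor strength is assumed.

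| Uptake with / without predictor | Power: unadjusted | Power: trigger | Power: always adjusted | Type I: trigger | Type I: always adjusted |
|---|---|---|---|---|---|
| 85% / 75% | 80.0% | 80.1% | 80.7% | 5.0% | 5.1% |
| 90% / 70% | 79.8% | 80.1% | 82.3% | 4.9% | 5.1% |
| 95% / 65% | 80.0% | 80.6% | 85.2% | 4.8% | 5.2% |

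**Cross-check by formula.** The unadjusted standardised distance to the margin is 0.10 / √(0.32/198) = 2.487. If the predictor explains a share R² of outcome variance, power is Φ(2.487/√(1 − R²) − 1.645). For 90% / 70%, R² = 0.10²/0.16 = 6.25%, giving Φ(0.924) = 82.2%, which agrees with the table. For 85% / 75%, R² = 0.05²/0.16 = 1.6%, giving 80.6%. For 95% / 65%, R² = 0.15²/0.16 = 14.1%, giving 85.0%.

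**Does the choice of estimate matter?** Under true equality, the always-adjusted and unadjusted analyses reached different non-inferiority conclusions in 2.9%, 5.8% and 8.9% of simulated trials for the three strengths. This shows why the governing estimate should be named. It does not measure harm done by the trigger itself.

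**The case against.** The strongest reply is that little goes wrong in practice, and much of it stands.

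- A reader might infer that testing and then adjusting raises the risk of a false non-inferiority claim. The simulation does not support this: type I error under the trigger is 4.8% to 5.0%.
- A reader might infer that an adjusted odds ratio would be set against an absolute margin. The protocol names no odds ratio. It names an absolute risk reduction with a confidence interval, which is on the margin's scale.
- A reader might call prior HIV testing a known predictor of uptake. The protocol only says it is collected. The size of the gain is therefore assumed, and with the weakest predictor simulated it is under one point of power.
- A reader might call the primary estimate a coin toss. The absolute risk reduction is stated without condition, so the unadjusted difference may always be produced, with adjustment added when triggered. What the text leaves open is which one decides.
- The 34% to 54% range is soft, because the baseline items are plainly related and the tested list is not given.

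The reply does not rescue the rule. It is stated in the protocol, so it is not a detail left to an analysis plan that is not shown. A descriptive baseline table is harmless; the fault lies in letting its P values choose the analysis.

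**Conclusion.** The point holds in a limited form. The trigger selects covariates by chance, omits any given prognostic one about 95% of the time, and leaves the deciding estimate unnamed. Fixed adjustment would give about 81% to 85% power at 198 per group, against about 80% under the trigger. That is a gain of 0.6 to 4.6 points, resting on the assumed predictor strength, its 50% prevalence and equal true uptake of 80%. The documents do not support a claim of inflated type I error or of an inadequate sample size.

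The argument applies directly to HIVST uptake, which is assessed in everyone randomised. It does not carry over unchanged to counseling among HIVST users. Users are a subset formed after randomisation, so their baseline differences need not be chance alone. The Background section also reports that every HIVST-OIC user in the earlier trial received counseling, so proportions may lie near 100%, where some regression models fail.

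This is a worthwhile, inexpensive improvement rather than a flaw that invalidates the design.

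**What to change.** In the Statistical analysis section, delete the P < .05 trigger; a descriptive baseline table may stay. Then state in advance:

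- **HIVST uptake.** The primary risk difference is adjusted for a short named list, such as baseline HIV testing/HIVST history, whatever the balance. Use a method that yields a risk difference with a confidence interval to compare with the 10-point margin, for example logistic regression with standardisation. Report the unadjusted difference as a sensitivity analysis.
- **Counseling among HIVST users.** Either the unadjusted risk difference is primary, or a method that is stable near 100% is named.

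The cost is a few sentences. The covariates are already to be collected ("history of HIV testing, COVID-19, and other sexually transmitted infections will be collected"), and the sample size does not change. The wording should be settled before outcome data are seen.
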